# Effects of a video-viewing intervention with positive word stimulation on the depressive symptoms of older patients with cardiac disease and subthreshold depression: a pilot randomized controlled trial protocol

**DOI:** 10.1186/s13030-024-00312-w

**Published:** 2024-07-16

**Keywords:** Subthreshold depression, Cardiac disease, Older adults, Mental health

## Abstract

**Background:**

Intervention for older patients with cardiac disease and subthreshold depression (StD) may be an effective strategy to prevent the development of major depressive disorder. The subliminal priming with supraliminal reward stimulation (SPSRS) website developed by us is an advanced intervention that can improve depressive symptoms in individuals with StD by presenting positive word stimuli in videos. However, its efficacy for treating depressive symptoms in older patients with cardiac disease and StD has not been investigated. Here, we present a pilot randomized controlled trial protocol to investigate the preliminary efficacy of an intervention for older patients with cardiac disease with StD.

**Methods:**

The study was designed as a single-center, open-label, pilot, randomized, parallel-group trial. The participants will include 30 older patients with cardiac disease and StD who are hospitalized in acute wards. The Experimental group received the SPSRS intervention (video viewing with positive word stimuli; n = 15) and the Control group will receive the YouTube intervention (video viewing without positive word stimuli; n = 15). In both groups, the intervention will be administered for 10 min per day, five times per week for 1 week. The primary outcome will be the change in the scores on the Japanese version of the Beck Depression Inventory-II at 1 week after the baseline assessment. The secondary outcomes will be the changes in the Specific Activity Scale, New York Heart Association functional classification, as well as grip strength at 1 week after the baseline assessment.

**Discussion:**

This pilot randomized controlled trial will be the first to evaluate the SPSRS intervention for depressive symptoms in older patients with cardiac disease and StD who are admitted to acute wards. The results will provide tentative indications regarding the impact of the intervention on depressive symptoms among older patients with cardiac disease and StD who are admitted to acute wards, and will contribute to the planning of a full-scale study.

**Trial registration:**

UMIN, UMIN000052155. Registered September 8, 2023, https://center6.umin.ac.jp/cgi-open-bin/ctr/ctr_view.cgi?recptno=R000059526. This study was registered with the University Hospital Medical Information Network (UMIN) (UMIN000052155) in Japan.

## Background

Both cardiac disease (e.g., coronary artery disease, heart failure, heart valve disease, and arrhythmia) and major depressive disorder (MDD) are prevalent worldwide and are projected to be major contributors to the global burden of disease through 2030, according to the World Health Organization [1]. Moreover, both conditions are important public health issues. MDD in patients with cardiac disease is a significant burden and a particularly important problem [2]. The prevalence of MDD among patients with cardiac disease is 15%–20% [3, 4], which is approximately twice that of the nonhospitalized general population [5]. Of particular importance, it has been suggested that cardiac disease and depression mutually increase each other’s risk [6], causing behavioral changes, such as decreased medication adherence [7], poor exercise capacity [8], and physical inactivity [9]. Therefore, this has been suggested to cause increased blood pressure, variability in heart rate, and arrhythmias [10, 11]. It is widely reported that MDD in patients with cardiac disease leads to increased cardiovascular events, more severe cardiac disease, decreased quality of life, mortality, and increased medical costs [12–18].

The aging of the population compounds these problems. As of 2019, the world population over 65 years of age was 703 million, and this figure is projected to increase to 1.5 billion by 2050, i.e., one out of every six people in the world [19], especially in developed countries, where the population is aging rapidly [20]. The American Heart Association predicts a significant increase in the prevalence of cardiac disease because of advanced age by 2030 [21]. Although the estimated prevalence of MDD among older adults is quite low (1%–4%) [22], it has been suggested that the prevalence of MDD in older adults admitted for medical treatment is 10%–12%, with an additional 23% of these individuals experiencing significant depressive symptoms [23]. This may accelerate the increase in the prevalence of MDD among older patients with cardiac disease, resulting in increased mortality, reduced quality of life, and increased health care costs.

Several intervention strategies have been proposed to address the various problems caused by MDD in older patients with cardiac disease. However, it has been suggested that MDD is less likely to be detected in this group of patients [24–26]. In addition, it has been suggested that approximately one-third of patients who are generally recognized to have MDD and receive treatment for it do not respond to current approaches, and more than half of those who develop MDD for the first time will have one or more relapses [27]. In particular, psychological and pharmacological interventions for cardiac disease populations have been reported to have significantly lower effect sizes compared with those observed for other chronic diseases, such as diabetes [28–30]. Furthermore, large trials, such as the landmark Enhancing Recovery in Coronary Heart Disease Patients study, have questioned the methodology and acceptability of MDD treatment in the population of patients with heart disease [31], as MDD treatment in these patients did not result in a significant reduction in major adverse cardiac events [32]. Given the high disease burden of MDD in these older patients with cardiac disease, the lack of awareness, and the ineffectiveness of current therapies, it is critical to implement early detection of, and preventive treatment for, at-risk patients. Preventive intervention for subthreshold depression (StD), which is a precursor symptom of MDD, may be an effective and cost-efficient approach [33–36].

Although StD does not meet the diagnostic criteria for MDD, it is characterized by clinically significant depressive symptoms [37]. It has been suggested that the prevalence of StD among patients with cardiac disease ranges from 17.0% to 27% [38–40]. Moreover, the number of people with StD is increasing in the older population [41, 42]. Even though StD is a precursor of MDD, it is known to cause decreased quality of life [37, 43], increased mortality [44, 45], poor health status [46], and increased health care costs [47]. Of particular importance is the fact that StD is a risk factor for the development of MDD [48, 49]. In fact, previous studies have suggested that 42% of patients with cardiac disease and StD will transition to MDD [39]. For these reasons, intervention strategies for StD should be established, and their effectiveness in preventing MDD development should be investigatedin older patients with cardiac disease and StD. To address the problems associated with StD, several preventive intervention strategies have been proposed to improve depressive symptoms specifically in patients with cardiac disease and StDs [50–52].

The use of antidepressants and other medications is common for treating MDD [53]. In addition, it has been suggested that, for patients with StD, the use of pharmacotherapy can have a positive impact by promoting an improvement in the overall depressive symptoms [53]. Conversely, a systematic review that investigated the effects of pharmacotherapy on StD did not find a significant reduction in depressive symptoms compared with the placebo [54]. In addition, it has been suggested that drug therapy can cause a variety of problems, including sexual dysfunction, hypotension, dizziness, insomnia, and appetite changes [55]. In addition, it has been proposed that the use of pharmacotherapy also increases the risk of myocardial infarction and other adverse events in patients with cardiac disease [56, 57]. Furthermore, patients with cardiac disease may have lower rates of medication adherence [7]. These problems regarding drug therapy may limit its use in older patients with cardiac disease and StD. Exercise therapy for MDD may also be an effective intervention to improve depressive symptoms [58, 59]. In addition, exercise therapy for patients with cardiac disease and MDD may reduce depressive symptoms [60, 61], and may decrease depressive symptoms in patients with StD [62]. However, it may be difficult from a medical safety standpoint to implement aggressive exercise therapy and other measures among older patients immediately after the onset of cardiac disease. Because of the problems associated with these existing interventions, interventions that are specifically designed to reduce depressive symptoms in older patients with cardiac disease and StD are needed. Therefore, the video replay website called subliminal priming with supraliminal reward stimulation (SPSRS) developed by us may be an effective intervention strategy to reduce depressive symptoms in older patients with cardiac disease and StD [63].

SPSRS is a video playback website that displays positive word stimuli in videos to improve depressive symptoms in patients with StD [63, 64]. The SPSRS tool features a website that allows patients to access it, search for videos by entering keywords, and watch the videos. In addition, SPSRS is free of charge and uses the YouTube Application Programming Interface, which allows patients to select from a wide variety of videos of interest and work toward reducing depressive symptoms. Previous studies have suggested that the use of SPSRS among individuals with StD compared with no intervention not only improves their depressive symptoms [64], but may also improve depressed mood immediately after the 10-min intervention [65]. In addition to the existing studies showing the effectiveness of SPSRS interventions in reducing depressive symptoms in patients with StD, one of the major factors that renders SPSRS applicable to older patients with cardiac disease is that it allows them to work toward reducing depressive symptoms without moving from their bed. Previous studies have suggested that video viewing can be performed with relatively low physical effort (1.0 to 1.5 Mets) when performed in the supine or end-sitting position [18, 66]. Therefore, SPSRS may be a safe approach to reduce depressive symptoms in older patients with cardiac disease who have difficulty performing high exercise loads. Given the limitations of these existing interventions (potentially for adverse events and difficulty of implementation) and the potential of SPSRS (potentially reducing depressive symptoms in people with StD and the relatively low loadings of 1.0–1.5 Mets that can be introduced), a randomized controlled trial (RCT) investigating the efficacy of SPSRS in older patients with cardiac disease and StD. However, no interventional studies have been conducted to examine the effects of SPSRS among older patients with cardiac disease and StD.

The Medical Research Council methodological framework was adopted to evaluate the effectiveness of the SPSRS intervention in older patients with cardiac disease and StD [67]. This methodology includes development, feasibility, piloting, evaluation, and implementation phases [67]. The feasibility and piloting phases are presented in the present study. Pilot studies are the best approach to assess the feasibility of larger, more expensive trials. Moreover, conducting pilot studies before larger trials helps to inform on the optimal design and scale and increases the likelihood of success [68]. Therefore, the purpose of this study was to present a protocol aimed at investigating the preliminary efficacy of the SPSRS intervention for depressive symptoms among older patients with cardiac disease and StD.

## Materials and methods

### Trial design and study setting

The study was designed as a single-center, open-label, pilot, randomized, parallel-group trial. The participants in this study will be older patients with cardiac disease and StD who are admitted to acute wards. We will compare the effects of a video-viewing intervention using the SPSRS (with positive word stimulation) and a video-viewing intervention using YouTube (without positive word stimulation). The Fujioka General Hospital is a public hospital that specializes in the treatment and rehabilitation of disuse syndrome, musculoskeletal disorders, cerebrovascular disorders, respiratory disorders, cardiovascular disorders, cancer, and pediatric disorders. The acute wards of the Fujioka General Hospital provide individual therapy performed by physical therapists (PTs), occupational therapists (OTs), and speech therapists (STs) to promote activities of daily living and independence to leave home among these patients. The acute wards at the Fujioka General Hospital provide individual therapy delivered by PTs, OTs, and STs for a maximum of 6–9 units per day (1 unit = 20 min), 7 days per week, 365 days per year. All patients admitted to these acute wards will be assigned a specific PT, OT, or ST. An alternate PT, OT, or ST may provide rehabilitation services when the assigned PT, OT, or ST is absent or unable to intervene. To prevent biases associated with the study design, this protocol followed the Standard Protocol Items: Recommendations for Interventional Trials (SPIRIT) 2013 statement [69].

### Eligibility criteria

Those who meet the following eligibility requirements will be selected as participants in the study.

#### Inclusion criteria

Men and women.Patients admitted to the acute wards of the Fujioka General Hospital.Individuals aged 65 years or older.Patients with cardiac disease (coronary artery disease, heart failure, heart valve disease, and arrhythmia).Patients with a total score of 10 or more on the Japanese version of the Beck Depression Inventory-II [70].Persons with sufficient cognitive ability to understand the content and purpose of the research.Persons who provided written consent before participation in this study.Patients with New York Heart Association functional classification (NYHA classification) degrees I–III.

#### Exclusion criteria

Individuals who have been diagnosed with a mental disorder at least once in their lifetime, regardless of the type of mental disorder.Patients currently receiving professional treatment for mental health issues.Individuals with visual or hearing impairments that interfere with daily living. Patients assessed by the Mini-international Neuropsychiatric Interview (M.I.N.I.) as having had a major depressive episode in the last 2 weeks [71].Patients with serious life-threatening complications (severe organ failure, respiratory disorders, cerebrovascular disorders, and musculoskeletal disorders).

The assessment of auditory, visual, and cognitive function, as well as impairment for the study is at the discretion of the therapist [72]. These parameters will be determined based on the patient’s response to verbal instructions during the administration of the Japanese version of the Mini-Mental State Examination (MMSE-J) and other assessments, and on the patient’s ability to recognize the objects used [72].

### Interventions

#### Experimental group

The Experimental group will receive a video-viewing intervention using SPSRS. The SPSRS tool is designed to present confidence-boosting words in the video for 17 ms, followed by 150 ms of positive words (Fig. 1). The confidence-boosting words are “can,” “let us try,” “good luck,” “able,” and “do not worry,” which appear randomly in the four corners of the screen [73]. The positive words are “nice,” “great,” “fantastic,” “satisfactory,” and “enjoyable,” and appear randomly in the center of the screen [74]. These words are presented repeatedly every 5 s. An iPad will be used as the medium for video viewing, which will be conducted with the researcher in attendance. SPSRS is used according to the operating manual. After accessing the SPSRS website using a researcher-controlled iPad, the participants will search for videos of interest and watch a 10-min video in the presence of the researcher (Fig. 2). If there is no video that the participant wants to watch, the researcher will suggest a video and watch it with the participant’s approval. The participants will watch the 10-min videos once per day, five times per week for a total intervention time of at least 50 min. The video-viewing time in this study was determined based on a previous study that examined the effects of the SPSRS intervention on patients with StD [64].

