#### Control group

The participants in the Control group will receive a total of at least 50 min of intervention per week, with 10 min of video viewing once per day, five times per week, for a total of at least 50 min per week, after accessing the YouTube website using a researcher-controlled iPad to search for videos of interest to them. If there is no video that the participant wants to watch, the researcher will suggest a video and watch it with the participant’s approval, as described for the Experimental group. The Control group videos will not show confidence-boosting or positive words; the Control group will use the same iPad as did the Experimental group.

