### Blinding

It will be difficult to blind the study participants and intervention providers because the Experimental and Control group interventions are distinctly different. In addition, the small number of research staff who will participate in this study renders it difficult to maintain rater blinding. Therefore, this study is planned as an open-label trial.

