## Discussion

This study is a pilot RCT aimed at investigating the effect of the SPSRS intervention on depressive symptoms in older patients with cardiac disease and StD who are admitted to acute wards. StD is a risk factor for increased mortality, incidence, rehospitalization rates, and severity of illness among older patients with cardiac disease. However, it has been suggested that the existing treatments, such as pharmacotherapy, for older patients with cardiac disease and StD do not adequately reduce depressive symptoms [32, 97–99]. Therefore, there is a need to identify alternative approaches for treating depressive symptoms in older patients with cardiac disease. The SPSRS website may be a new intervention strategy that can improve depressive symptoms in older patients with cardiac disease and StD. The SPSRS is a video-viewing website in which positive language stimuli are presented, and can be accessed through any Internet-enabled device. Therefore, the SPSRS intervention is less burdensome for the patients and interveners; has a low cost; is simple, novel, and guaranteed to be of similar quality for all participants; and can provide treatment to various individuals. Therefore, we designed a pilot RCT to investigate the preliminary efficacy of the SPSRS intervention among older patients with cardiac disease and StD. This pilot RCT was designed to enhance the scientific validity of full-scale RCTs. The results of this study will provide additional insights into the preliminary effectiveness and feasibility of the SPSRS intervention, and will allow us to identify the modifications and improvements that are necessary for a successful larger RCT.

This study has several strengths. First, this is the first pilot RCT to investigate the preliminary efficacy of the SPSRS intervention for improving depressive symptoms in older patients with cardiac disease and StD who are admitted to acute wards. This pilot RCT may lead to the development of a state-of-the-art treatment approach to improve depressive symptoms in older patients with cardiac disease presenting with StD, and can expand our knowledge of the benefits and limitations of intervention strategies for the management of depressive symptoms in this specific population. Second, the study has a high external validity, because it includes patients suffering from a variety of cardiac diseases.

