This study also had several limitations. First, this study will be conducted on an open-label basis because of its nature. This may lead to a bias among the treatment providers, study participants, and evaluators. When interpreting the study results, it will be necessary to consider the effects of other factors, such as participant expectations and the relationship between the treatment provider and the patient, on depressive symptoms. Second, because this is the first study to examine the effect of the SPSRS intervention on older patients with cardiac disease and StD who are admitted to acute wards, no formal sample size calculations will be performed. This limitation may reduce the statistical power of the primary and secondary outcomes. Third, because this pilot RCT will be conducted at a single site exclusively, the sample is less representative, and not all findings obtained will apply to older patients with cardiac disease and StD who are admitted to acute wards [100]. Fourth, this study may underestimate the effects of SPSRS intervention on depressive symptoms in older patients with cardiac disease and StD. The intervention duration in this study was 1 week because the number of days of hospitalization should be considered in the acute care of patients with cardiac disease in Japan and the feasibility of data collection and the duration of possible rehabilitation intervention. The BDI-II is a self-report measure of depressive symptoms that assesses symptoms over the past 2 weeks; however, previous studies indicate that a 1-week intervention period can produce significant differences in the BDI-II [87–89, 101, 102]. For these reasons, we employed BDI-II in this study. However, considering that the BDI-II is a self-report measure of depressive symptoms that assesses symptoms over the past 2 weeks, we cannot dismiss the possibility that the intervention period of this study (one week) will result in little changes in depressive symptoms as measured by BDI-II. Finally, because the specific video to be viewed during the SPSRS is determined based on participant self-selection from a full range of videos, the differences in the participants’ video choices may have an impact on depressive symptoms.

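### When a participant wants no particular video, a researcher who knows the allocation suggests one, and no selection rule common to both arms is stated, so suggested content could differ by arm

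*Protocol article*

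**What the plan says.** Under Interventions, the Experimental group searches for videos on the SPSRS site and the Control group does so on YouTube, on the same iPad, with the same session length and frequency. The fallback for the Experimental group is: "If there is no video that the participant wants to watch, the researcher will suggest a video", which is then watched subject to the participant's approval. For the Control group the rule is carried over by reference: "the researcher will suggest a video and watch it with the participant’s approval, as described for the Experimental group". In the Experimental group section, viewing is on an iPad, "which will be conducted with the researcher in attendance". Neither section gives a list, a category or a matching rule for suggested videos.

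The Blinding section explains: "It will be difficult to blind the study participants and intervention providers because the Experimental and Control group interventions are distinctly different". It adds that blinding of raters is also impractical, and concludes: "Therefore, this study is planned as an open-label trial".

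The limitations in the Discussion say that differences in participants' "video choices may have an impact on depressive symptoms", and give self-selection as the cause. A separate limitation says in general terms that open-label conduct may bias providers, participants and evaluators. Data collection records the types of video viewed in both groups. It does not mention who chose them. The model under Statistical methods has group, time and their interaction as fixed effects, with nothing for content or chooser.

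**The concern.** The trial compares viewing with positive words against viewing without them. The control is well built to isolate the words, since device, session length and frequency match. What a participant picks unprompted is part of the intervention as designed. A suggestion is different: it comes after allocation, from someone who knows the arm, in a team that developed SPSRS. Randomisation cannot balance a choice made after it and with knowledge of it.

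If suggestions in one arm tended to be more cheerful or engaging, the difference would enter the BDI-II comparison and look like an effect of the words. It would also enter the Hedges' g that the article plans to report from a pilot meant to inform a full-scale trial. The stated limitation on video choice does not reach this route, because it names only the participant as chooser.

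**Working it through.** **Reading the sections together**

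1. Who chooses: normally the participant; in the fallback, the researcher proposes and the participant accepts or declines (Interventions, both groups).
2. What the proposer knows: the allocation (Blinding). The concealment described under Allocation concerns the assignment process and does not cover sessions delivered afterwards.
3. Whether content matters: the article says it may (Discussion, limitations).
4. What limits a difference between arms: the participant's approval, which is a veto and does not equalise content across arms. Recording video types allows an imbalance to be described later but does not prevent it.

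The route to bias therefore exists. Its size depends on two quantities that the documents do not give.

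**Scale, under assumptions**

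The plan has no figure on this point to reproduce. Its sample size rests on a pilot rule of thumb, and only 2 × 15 = 30 can be checked; it agrees.

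From the article: n = 15 per arm, 5 sessions per participant, two-sided alpha 0.05.

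Sessions per arm: 15 × 5 = 75. If 10% to 40% needed a suggestion (assumed), that is 7.5 to 30 sessions per arm.

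Assumed quantities:
- f = share of viewing that is researcher-suggested.
- c = between-arm difference in outcome, in SD units, that would arise if all viewing were suggested.

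Bias in the standardised between-arm difference = f × c, taking the effect as proportional to the share.

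Rejection rate with no true effect of the words: two-sided t comparison with df = 2 × 15 − 2 = 28 and noncentrality f × c × √(15/2). This stands in for the planned mixed model.

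| f | c (SD) | Bias (SD) | Rejection rate |
|---|---|---|---|
| 0.10 | 0.2 | 0.02 | 5.0% |
| 0.10 | 0.5 | 0.05 | 5.2% |
| 0.25 | 0.2 | 0.05 | 5.2% |
| 0.25 | 0.5 | 0.125 | 6.3% |
| 0.50 | 0.2 | 0.10 | 5.8% |
| 0.50 | 0.5 | 0.25 | 10.1% |
| 1.00 | 0.2 | 0.20 | 8.3% |
| 1.00 | 0.5 | 0.50 | 26.2% |

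For comparison, 15 per arm gives 80% power only for a difference of about 1.02 SD (normal approximation) or 1.06 SD (t-test). With modest fallback use, the false-positive rate barely moves from 5%. The bias in the effect estimate is the more relevant quantity for a pilot.

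**The case against.** The strongest reply is that the rule is worded alike in both arms and that the participant must approve. An imbalance then requires the researcher to apply one rule differently by arm, and nothing in the article shows that this happens. The fallback also operates only after the participant has found nothing wanted. This stands. A reader might infer that the researcher chooses freely and without constraint, or that content will in fact differ. The text supports neither. It supports only that content could differ, because approval does not make the two arms' suggestions alike.

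Second, the SPSRS operating manual is cited but not shown, and the figure on the SPSRS procedure is missing. Either could hold a selection rule. This also stands as a caution. No manual is cited for YouTube viewing, although the control fallback refers back to the experimental one. The point made here is about the discretionary method the article describes, and does not depend on a missing detail.

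Third, the limitations already concede provider bias. They do so in general terms and do not connect it with video content, so the disclosure is partial.

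Fourth, the size rests wholly on assumed values, and the trial is a pilot of 30 seeking tentative indications. Both are true, and they limit the weight of the point.

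A reader might also see a contradiction in the Discussion's description of SPSRS as "guaranteed to be of similar quality for all participants". The phrase describes the website as a delivery tool. It does not claim that content is balanced between arms, so nothing is built on it here.

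**Conclusion.** The concern holds in a limited form. The article fixes a fallback in which an unblinded researcher suggests content, states no selection rule shared by the arms, and accepts that content may affect depressive symptoms while naming only participants as the source. This leaves an avoidable post-randomisation route by which content could differ by arm and be read as an effect of the words.

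The size cannot be derived from the documents. On the assumed range it runs from 0.02 SD, which is negligible, to 0.25 SD if half of viewing is suggested and the content difference is 0.5 SD. The value of 0.50 SD needs every session to be suggested and is an upper extreme. If the fallback is rarely used, the effect is small. The case for acting rests on the low cost of closing the gap and not on evidence that bias will occur.

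**What to change.** 1. In both arms, replace discretionary suggestion with one common list of videos of about 10 minutes, specified in advance and playable on both sites. Offer items in the same fixed order, moving to the next if one is declined. This should be feasible because SPSRS draws on YouTube through its programming interface (Background).
2. Record each session as *own choice* or *list*. This measures the unknown share f, which is useful feasibility information for a larger trial.
3. Extend the limitation on video choice to videos suggested by the researcher.

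The study period was set to start in October 2023. If recruitment has begun, introduce the change by amendment through the two ethics committees named in the article, and note which participants were treated before it.

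Cost: drawing up one list and adding a tick box to the session record. Downside: suggestions are less tailored for participants with no preference, equally in both arms. The fix is partial. Declined items could still lead to some difference in what is watched, and self-chosen content is unaffected.
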